#### 4 TRIAL OBJECTIVES AND PURPOSE

The **overarching purpose** of a future main trial is to determine the clinical- and cost-effectiveness of adding a stratified care intervention to usual care designed to improve outcomes of rehabilitation care for older adults after hip fracture. Several uncertainties will first be addressed through a randomised feasibility trial which this protocol details.

The **primary objective** of this feasibility and pilot randomised trial is to determine the treatment fidelity of the proposed intervention. **Secondary objectives** seek to determine:

1. Count of screened, eligible, approached, recruited, and retained participants and carers.
2. The acceptability of the intervention to participants, carers, and therapists.
3. Barriers and enablers to intervention delivery.
4. Acceptability, completeness, and descriptive comparison of patient reported outcome data collection.
5. Count of inadvertent unblinding of outcome assessors.
6. Count of AE and SAE.
7. Indicative sample size for a definitive trial.

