#### **c) Self-managed exercise programme:**

Progressive exercise programme inclusive of resistance and endurance training tailored to functional baseline based on programme based on a published exercise training programme and as specified in Box 1 below, taught by a therapist who will populate a training plan template for the participant, which they can implement independently. Up to three additional sessions for monitoring and progression by a therapist.

Box 1: Progressive resistance and endurance training programme.

|                                        |   | Type                        | Description                            | Individually Tailored                                                                                                                                                                                                                                 |                                                                                                                                                                                                                                                                                                           |
|----------------------------------------|---|-----------------------------|----------------------------------------|-------------------------------------------------------------------------------------------------------------------------------------------------------------------------------------------------------------------------------------------------------|-----------------------------------------------------------------------------------------------------------------------------------------------------------------------------------------------------------------------------------------------------------------------------------------------------------|

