### **a) Education**

1. Participants provided with information pack detailing what to expect from rehabilitation and their recovery.
2. Content discussed over first week (paced and reinforced) by therapist with participant and/or their carer (as available). Points to cover in discussion include:
  - i. Getting better after surgery to fix a broken hip.
    - What does 'getting better' mean to the participant and/or carer. Discuss how rehabilitation is designed to support this.
  - ii. Who is involved?
    - Focus on the participant, carer, and therapy team.
  - iii. What happens in hospital?
    - Whether their pain is appropriately managed. If related to pain, discuss usual care process for requesting pain management prior to moving/ activities. Discuss any barriers to this request and how can rectify.
    - Whether they are feeling afraid of moving/activities due concerns about falls. If so, reinforce (regularly) that this is normal but that engaging in mobility/activities as able is the best thing they can do for themselves. Provide positive feedback on moving/activity achievements at regular intervals.
    - Whether the participant's ability to think or remember clearly is different since their operation. If concerns, explore and relay findings to multidisciplinary team.
    - Why it is important for them to do as much as they can for themselves safely in hospital. Discuss need to reinforce what is completed during supervised sessions in their own time (if therapist deems it safe to do so).
    - Discharge planning and whether the participant and/or carer feels they are involved in decision making. If not, why not, and how can rectify.
  - iv. What happens after hospital?
    - Discuss likely care pathway including waiting times.
    - Discuss what they can be doing for themselves while they wait.
  - v. What about later?
    - Manage expectations for the likely extent of therapy input once discharged from hospital and need to consider engagement with other services including charities to continue their recovery.

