### **c) Enhanced assessment**

1. Assessment of pain with the Algoplus dementia friendly pain scale from the first therapist contact and all contacts going forward.
2. Assessment of depression by the therapist using the Cornell Scale for Depression in Dementia. This should only be completed for participants with no prior depression diagnosis. The scale has two parts - one to be responded to by the participant's carer and the second by the participant themselves. The scales require responses based on 'the last week'. This should be completed following the first week in hospital. If the final score suggests a probable/definite major depression, notify multidisciplinary team, and suggest psychiatry referral.
3. The therapist will determine whether the participant has an advanced care plan (from medical chart/medical team). If there is no advanced care plan in place, refer to specialty who is responsible for supporting creation of an advanced care plan e.g. general practitioner following discharge
4. Prior to participant discharge. Ensure handover of pain history, depression assessment, and whether a new advanced care plan was established, to community team.

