## **8.6 Detailed Description**

The 'stratify-hip algorithm' is an algorithm available at <https://stratifyhip.co.uk/>. We will combine this algorithm with a clinical protocol based on subgroup assignment. Therapists will navigate to the website. There they will enter five pieces of information related to a potential participant – age (5-year category), sex (male, female), prefracture ambulation (outdoor and indoor, indoor only, no ambulation), prefracture residence (home, nursing/residential care), dementia status (yes, no). Following entry of this information a 'combined outcome risk' for death and change in residence is generated. This will assign patients to a low, medium, or high risk subgroup. Potential participants who consent and are randomised to the intervention arm of the study will receive an intervention tailored to their subgroup assignment. The low risk subgroup will receive a self-managed exercise programme in addition to usual care. The medium risk subgroup will receive education, a goal-orientated mobility programme (with carer training as available), and early enhanced discharge planning. The high risk subgroup will receive education, enhanced assessment, orientation, and a goal-orientated activities of daily living programme (with carer training as available). See section 7.8 for further detail on the clinical protocol.

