## **14 STATISTICAL CONSIDERATIONS**

### **14.1 *Sample size***

The sample size was determined in consultation with the trial statistician. The recruitment target of 60 participants aims to have sufficient participants to provide the operational experience to plan a definitive trial; provide reasonably robust estimates of our feasibility outcomes; and to estimate the variability of the proposed patient outcomes to inform a future sample size calculation. A recruitment target of 60 participants (30 per treatment arm) will allow overall retention rate at 12-weeks to be estimated with precision of  $\pm 11\%$ , using an exact 95% confidence interval, from previously observed retention rates of  $\sim 80\%$  for the same population. Assuming a non-differential retention rate of 80% at 12-week follow-up, this target will provide follow-up outcome data on  $\sim 24$  participants per arm.

This required sample size will be attainable in practice. In 2022, 255 patients were admitted to a hospital ward at St Thomas's Hospital with hip fracture. Previous trials of patients with hip fracture reported recruitment rates of 32% in hospital.

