### **Figure 2: Progression criteria**

|                          | GO                                                              | AMEND                                                             | STOP                                                            |
|--------------------------|-----------------------------------------------------------------|-------------------------------------------------------------------|-----------------------------------------------------------------|
| Recruitment       | ≥40% eligible                                                   | 21-39% eligible                                                   | ≤20% eligible                                                   |
| Recruitment       | ≥50% eligible recruited                                         | 31-49% eligible recruited                                         | ≤30% eligible recruited                                         |
| Randomisation     | ≥70% of those recruited randomised                              | 49-70% of those recruited randomised                              | ≤48% of those recruited randomised                              |
| Fidelity          | ≥80% sessions included all intervention components as described | 51-79% sessions included all intervention components as described | ≤50% sessions included all intervention components as described |
| Outcome, 12-weeks | ≥80% completeness of EQ5D at 12-week follow-up                  | 51-79% completeness of EQ5D at 12-week follow-up                  | ≤50% completeness of EQ5D at 12-week follow-up                  |

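### The fidelity progression criterion counts sessions containing all components, but section 7.7 spreads the components across sessions, so read as printed it would score perfect delivery as STOP

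*Protocol*

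**What the plan says.** Protocol section 4 states that the primary objective "is to determine the treatment fidelity of the proposed intervention". Section 14.4 offers progression criteria in Figure 2. The fidelity row sets GO at "≥80% sessions included all intervention components as described", AMEND at 51-79%, and STOP at "≤50% sessions included all intervention components as described". No other numerical threshold for fidelity is given.

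Section 7.7 describes what is to be delivered:

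- **Low risk (7.7.1):** a self-management review, advocacy training and a taught exercise programme, followed by "Up to three additional sessions for monitoring and progression by a therapist".
- **Medium risk (7.7.2):** education, with "Content discussed over first week (paced and reinforced) by therapist with participant and/or their carer (as available"; goal setting; up to five mobility training sessions; a 30-minute one-to-one carer training where a carer is available; and discharge planning.
- **High risk (7.7.3):** education on the same first-week pacing; orientation; pain assessment at every contact; a depression scale for those without a prior diagnosis ("This should be completed following the first week in hospital"); a handover before discharge; up to three activities-of-daily-living sessions; and carer training where available.

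The extra therapist time is budgeted per participant: 1 h 40 min (low), 2 h 15 min (medium) and up to 2 h 45 min (high). Section 12.1 says a treatment log is completed after each supervised session.

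**The concern.** The criterion asks whether a session held the whole package. The intervention is built so that most sessions hold only part of it: exercise progression in one, a portion of the education in another, discharge planning near the end. A low-risk participant's first session could contain all three low-risk components. A medium- or high-risk session is not designed to contain everything, because some items are paced over a week or fixed to its end or to discharge.

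At stake is the go/no-go signal on the primary objective. On the printed wording, a faultlessly delivered intervention would be classed as STOP. On a looser reading, the score depends only on sessions that took place, so it could show GO while some intervention participants received nothing.

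**Working it through.** **1. Does the package recur within each session?** The time budgets say not. Repeating the medium-risk package at each of five mobility sessions would take 5 × 135 min = 675 min = 11 h 15 min, against the 2 h 15 min budgeted per participant.

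**2. Score under perfect delivery, printed wording.**

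Inputs: 30 participants in the intervention arm (14.1); 20 per subgroup (7.2), so about 10 per subgroup in that arm; a cap of 12 per subgroup per arm (7.6); session maxima from 7.7. A low-risk participant contributes at most one complete session, the first. A medium- or high-risk participant contributes none.

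Score = n_L / (n_L·s_L + n_M·s_M + n_H·s_H), where n is participants and s is sessions per participant.

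| Assumption | n (L/M/H) | s (L/M/H) | Score |
|---|---|---|---|
| Named sessions at their maxima | 10/10/10 | 4/5/3 | 10/120 = 8.3% |
| Further medium- and high-risk sessions for education, goals, carer training and discharge | 10/10/10 | 4/8/6 | 10/180 = 5.6% |
| Few sessions | 10/10/10 | 1/2/2 | 10/50 = 20% |
| Few sessions, low risk at its cap | 12/9/9 | 1/2/2 | 12/48 = 25% |
| One session each, low risk at its cap | 12/9/9 | 1/1/1 | 12/30 = 40% |

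The last row is a ceiling, not a realistic case. The numerator cannot exceed 12 under the cap, and with 30 participants each seen at least once the denominator cannot be below 30. All results are at or below 50%, which is STOP.

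The low-risk group alone scores 100%, 50%, 33% or 25% with 0, 1, 2 or 3 additional sessions. The failure therefore concerns the overall score and the other two groups, not every individual.

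**3. Score under the reading 'components due at that session'.** Perfect delivery gives 100%, which is GO. But take, as an illustration, 15 of 30 intervention participants with no session and the other 15 with sessions that were all complete. The session score is still 100%, whereas the share of participants who received their package is 15/30 = 50%. Section 14.2 says all analysis selects participants by intention to treat, and a sessions-held denominator does not do that.

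**4. Precision.** The plan's own figure reproduces. For retention of 48/60, the exact (Clopper-Pearson) 95% CI is 67.7% to 89.2%, a half-width of 10.8 points, matching ±11%. For a participant-level fidelity measure at the GO threshold, 24/30, the exact CI is 61.4% to 92.3%, a half-width of about 15 points.

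**The case against.** The strongest reply is that the criterion says the components are included as described, and 7.7 describes them with their timing and conditions. A session could then count as complete when it held what was set for it. The protocol does treat sessions as content-specific: 7.6 separates therapist-led sessions from carer training sessions, and 7.7 names mobility and daily-living training sessions. This reading is plausible and may be what was meant. It is not written down, however. Figure 2 refers to no schedule of what is due, and the session counts are maxima. The flow figures in 7.7 and the treatment log form are not shown here and might map components to time, so it cannot be said that no such schedule exists, only that the criterion does not point to one.

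A second reply is that scoring rules belong in the statistical analysis plan. That is true of detail such as handling conditional items. But the protocol has itself fixed the unit and the cut-offs, and as printed they do not match the intervention.

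Three stronger inferences are tempting and not supported:

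- **That the trial cannot answer its primary question.** Logs, diaries, observed sessions and interviews all feed fidelity (5.1, 7.6, 12.1), and 14.3 summarises it by arm and subgroup. The defect is in the decision rule.
- **That the sample-size precision is wrong.** Section 14.1 says the target "will allow overall retention rate at 12-weeks to be estimated with precision of" ±11%. That is a claim about retention only, and it is correct.
- **That 8.6 contradicts 7.7.1 in substance.** Section 8.6 says "The low risk subgroup will receive a self-managed exercise programme in addition to usual care", omitting two components. It is a short device description that refers the reader elsewhere for the clinical protocol, so the mismatch is editorial.

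**Conclusion.** The point stands as a mismatch between the fidelity criterion's wording and the intervention it measures. On the printed wording, perfect delivery scores about 6% to 40%, always STOP. The exact percentage rests on assumed session counts, but the band does not, given 30 intervention participants, the cap of 12 per subgroup and at least one session each.

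A reader might infer that the trial is bound to end in STOP. The documents do not support that, because the result holds only on the literal reading and the alternative gives 100%. What they do support is that two readings of one sentence lead to opposite decisions on the primary objective, and that neither deals with intervention participants who had no session. This should be settled before delivery data accumulate. Section 14.2 requires the analysis plan only before database lock, while treatment logs are monitored during the trial (11.3) in a database whose users are not blind to allocation (12.2).

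**What to change.** Restate the fidelity row of Figure 2:

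- **Unit and denominator:** the participant, over everyone randomised to the intervention arm, including those with no session.
- **Numerator:** participants who received all applicable components of their subgroup package, as described in 7.7, by discharge, taken from the treatment logs. Conditional items, such as carer training, count only when applicable.
- **What counts as received:** the trial team should state this for each component. Accepting a single log entry would be too lenient: one of up to five mobility sessions would then pass as full delivery, and an item specified for every contact would pass on one.
- **Alongside it:** the session-level percentage, defined explicitly as all components due at that session.
- **Bands and precision:** confirm that 80 / 51-79 / 50 are still the intended cut-offs for the new unit, and report the exact 95% CI.

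The low-risk summary in 8.6 can be aligned with 7.7.1 in the same amendment. Section 14.1 needs no correction.

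The cost is a wording change using logs already planned, with no change to treatment, visits or sample size. The drawback is imprecision: with about 30 participants, an observed 80% carries an interval of 61% to 92%.

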### 6.1 Participant inclusion criteria

We will include adults

- aged 60 years or more.
- admitted to hospital for surgical repair of a low energy hip fracture.
- who are willing and able to provide consent or assent depending on the level of cognitive impairment.

We sought to employ as inclusive eligibility criteria as possible to maximize representativeness of the population (and to ensure that the intervention is assessed for patients in all three risk subgroups). This decision followed our PPI consultations and findings from our systematic review detailing inequities in access to trials of rehabilitation after hip fracture surgery (27.3% of potential participants of 35 trials were excluded based on factors that stratify healthcare opportunities and outcomes).

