|                 | Walk indoors accompanied by another person and using two crutches while completing a series of cognitive tasks e.g., reciting every other letter of the alphabet, counting to 100 in increments of 5. |

2. Up to five mobility training sessions with progressions (See Box 3 for example of progressions).

Box 3: Example of progressions towards behaviour goal

|                                                                                                                     |                                                                                                                    |
|---------------------------------------------------------------------------------------------------------------------|--------------------------------------------------------------------------------------------------------------------|
| Behaviour goal                                                                                                      | Walk continuously indoors on flat ground for 3 minutes with the use of two crutches independently.                 |
| Progressions
towards goal
[figure not shown] | Walk continuously indoors on flat ground for 3 minutes with the use of two crutches accompanied by another person. |
|                                                                                                                     | Walk continuously indoors on flat ground for 3 minutes with the use of two crutches accompanied by another person. |
|                                                                                                                     | Walk continuously indoors on flat ground for 3 minutes with the use of a frame independently.                      |
|                                                                                                                     | Walk continuously indoors on flat ground for 3 minutes with the use of a frame accompanied by another person.      |

3. Progress chart template completed and placed at bedside indicating to the participant what they can complete independently and/or what they should be supported by team (including carer) to complete.
4. Carer (as available)

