2. Up to three activity of daily living training sessions with progressions and aids (as needed e.g., reaching aid, bed rail, raised toilet seat) (See Box 5 for example of progressions).

| Box 5: Example of progressions towards behaviour goal                                                          |                                                                                                                                      |
|----------------------------------------------------------------------------------------------------------------|--------------------------------------------------------------------------------------------------------------------------------------|
| Behaviour goal                                                                                                 | In a seated position, lift left thigh without use of hands and hold for 5 seconds following verbal direction, repeat for right thigh |
| Progressions
towards goal [figure not shown] | In a seated position, lift left thigh and hold without use of hands for 3 seconds following verbal direction, repeat for right thigh |
|                                                                                                                | In a seated position, lift left thigh and hold without use of hands for 1 seconds following verbal direction, repeat for right thigh |
|                                                                                                                | In a seated position, lift left thigh and lower with control without use of hands following verbal direction, repeat for right thigh |
|                                                                                                                | In a seated position, lift left thigh without use of hands following verbal direction, repeat for right thigh                        |

3. Progress charts template completed and placed at bedside indicating to the participant what they can complete independently and/or what they should be supported by team (including carer) to complete.
4. Carers (as available)

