## **14.3 Quantitative analysis**

A CONSORT flow diagram will display data specifying counts of screened, eligible, approached, randomised, and completed enabling estimation of eligibility, recruitment, consent and follow-up rates. Confidence intervals for recruitment and retention rates will be produced to inform assumptions for planning the definitive trial. Rates of screened, eligible, approach and recruited will also be estimated for carers of participants enrolled into the medium- or high-risk intervention arm. Completion rates will be estimated for outcome measures collected at each time-point. Baseline characteristics will be summarised by allocated arm (and by subgroup assignment) with descriptive statistics (measures of central tendency and dispersion) to enable assessment of baseline comparability of arms (a degree of imbalance is anticipated in this small feasibility study). Patient-reported outcomes and treatment fidelity will be summarised by allocated arm (and by subgroup assignment) at each follow-up, with descriptive statistics (measures of central tendency and dispersion). Between-arm differences, including in changes from baseline, will be reported for the patient-reported outcomes with corresponding measures of dispersion to enable an assessment of sensitivity to change to inform primary outcome selection for a definitive trial and a formal power calculation for this outcome for a definitive trial.

For patients who do not speak English, the count of pseudo-anonymised patient-reported outcome measures circulated and returned by post will be documented. The content of the patient-reported outcome measure will be described narratively ensuring participant anonymity is preserved (the language versions circulated will not be specified in reporting).

The quantitative analysis will be completed by a trial statistician using R (<https://www.r-project.org/>) (or other well validated statistical packages) after database lock at trial end. The TSDMC will monitor screening/eligibility, approach and randomisation rates and safety reporting. There are no additional interim analyses planned. Qualitative analysis

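### The fidelity progression criterion has no subgroup condition, so it can read GO while one of the three matched packages is delivered at the protocol's own STOP level

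*Protocol*

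**What the plan says.** The primary objective "is to determine the treatment fidelity of the proposed intervention" (Protocol section 4). The only decision rule attached to fidelity is one row of Figure 2: GO when "≥80% sessions included all intervention components as described", AMEND at 51-79%, and STOP when "≤50% sessions included all intervention components as described". Neither the row nor section 14.4 mentions risk subgroup.

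What is delivered differs by subgroup (sections 7.7.1 to 7.7.3 and 8.6). The session limits differ too:
- Low risk: a taught exercise programme, then "Up to three additional sessions for monitoring and progression by a therapist".
- Medium risk: "Up to five mobility training sessions with progressions", plus education and discharge planning.
- High risk: "Up to three activity of daily living training sessions with progressions and aids", plus education, orientation and enhanced assessment.

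Elsewhere the design is organised by subgroup. Eligibility is kept broad partly "to ensure that the intervention is assessed for patients in all three risk subgroups" (section 6.1). Enrolment targets 20 per subgroup (section 7.2), randomisation is stratified by subgroup (section 7.4), and at least four therapist-led sessions are observed in each (section 7.6). Section 14.3 says that "treatment fidelity will be summarised by allocated arm (and by subgroup assignment) at each follow-up".

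**The concern.** A stratified intervention can be delivered only if each matched package can be. The criterion averages over packages, weighting each by the number of sessions it happens to generate. Nothing in the protocol justifies that weighting. Two well-delivered packages can outvote a third that meets the protocol's own definition of STOP. The progression table would then show GO on fidelity for an intervention of which one part was not delivered as described. The subgroup figures that would reveal this are planned, but they have no role in the decision.

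**Working it through.** **The plan's own figure.** Section 14.1 derives only the precision of 12-week retention. For 48/60 the exact 95% interval is 67.7% to 89.2%, an average half-width of 10.8 points, which agrees with the stated ±11%. No derivation is given for the fidelity bands.

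**Inputs.** Thirty participants per arm (section 14.1) and 20 per subgroup (section 7.2) give about 10 intervention participants per subgroup. Session counts are stated only as maxima, so the weights are assumptions:
- 4/5/3 (low/medium/high): the capped training sessions, taking the low-risk teaching contact as one session.
- 4/5/7: an assumed case in which high-risk generates the most contacts.
- Extra therapist time in sections 7.7.1 to 7.7.3: 100, 135 and up to 165 minutes, total 400.

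**Formula.** Overall fidelity = Σ(n × s × f) / Σ(n × s), where n is participants, s sessions each and f fidelity. If one package has weight w and fidelity 50%, the other two must reach (0.80 − 0.50w) / (1 − w) for the overall figure to be 80%.

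| Weighting | Low at 50% | Medium at 50% | High at 50% |
|---|---|---|---|
| 4/5/3 (w = 0.33, 0.42, 0.25) | others need 95% | 101% | 90% |
| Therapist minutes (w = 0.25, 0.34, 0.41) | 90% | 95% | 101% |
| Equal sessions (w = 0.33 each) | 95% | 95% | 95% |

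A value above 100% means that the package cannot be hidden on average. Worked example for 4/5/3: 36/40 + 45/50 + 15/30 = 96/120 = 80.0%, which is GO with high-risk at 50%.

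The subgroup split matters as well. Section 7.6 caps each subgroup at 12 per arm. With 4/5/3 sessions and high-risk at 50%, the others need 85% under a 12/12/6 split and 93% under 9/9/12.

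**Simulation.** Beta-binomial model, 10 participants per subgroup, within-participant correlation 0.1 (assumed), 60,000 replicates. Entries are the approximate chance of GO.

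| Sessions | True fidelity, low/medium/high | As written | With a 50% floor per subgroup | 80% required in every subgroup |
|---|---|---|---|---|
| 4/5/3 | 95/95/50 | 90% | 43-44% | under 1% |
| 4/5/3 | 95/95/40 | 70% | 12% | under 1% |
| 4/5/3 | 90/90/50 | 56% | 35% | under 1% |
| 4/5/3 | 85/85/50 | 21% | 17% | under 1% |
| 4/5/7 | 50/95/95 | 91% | 44% | under 1% |
| 4/5/7 | 95/95/50 | 11% | 11% | under 1% |
| 4/5/3 | 85/85/85 | 92% | 92% | 58% |
| 4/5/3 | 90/90/90 | 99.8% | 99.8% | 91% |

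The first entry moves only between 88% and 92% for correlations from 0.2 to 0.02.

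**Precision.** Treating sessions as independent, the exact 95% interval is 61% to 92% for 24/30 and 31% to 69% for 15/30. For 96/120 it is 72% to 87%.

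**The case against.** Four points can be made for the plan.

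- The protocol never says that sessions are pooled, and the level of the percentage could be settled in the analysis plan. However, Figure 2 itself fixes the rule, and one row without a subgroup condition is plainly read as one overall percentage.
- A failing package would not go unseen: section 14.3 summarises fidelity by subgroup, and section 7.6 observes sessions and samples interviews by subgroup. This stands, and it limits the harm. It does not link the subgroup result to the decision.
- The future trial would test stratified care as one strategy, so an overall criterion is defensible. That supports keeping the overall threshold, but not ignoring a package in the STOP band.
- Subgroups are small. This stands, and it decides the form of the fix.

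A reader might also infer two stronger things. The first is that the high-risk package necessarily carries the least weight and is the one hidden. The 3-in-12 weight counts only capped training sessions. That package also includes education, assessment and handover contacts and has the largest stated therapist time (165/400 = 0.41), at which it could not be hidden on average. The second is that GO would mean the primary objective had been declared met. The objective is to determine fidelity, and sections 4 and 5.1 meet it by analysing diaries, logs and observations, whichever band results.

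**Conclusion.** The point holds in a limited form. As written, the fidelity row can return GO with one package at or below 50%. This is possible rather than certain: in most layouts it needs the other two packages at about 85-95%, and the chance falls to about 21% when they are truly at 85% (4/5/3, high-risk at 50%). Which package is exposed cannot be read from the protocol, because session numbers are given only as upper limits. The 90% and 91% figures rest on assumed session counts, 10 participants per subgroup and a correlation of 0.1, so they illustrate the weakness and do not predict this trial. The weakness lies in the progression rule, not in the planned reporting, and it is cheap to correct.

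**What to change.** In Figure 2, keep the overall 80% threshold for GO on fidelity and add a second condition: no risk subgroup may be in the STOP band (50% or less). If one is, the fidelity result is AMEND for that package, whatever the overall figure. Report the three subgroup percentages with exact confidence intervals beside the overall one.

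This is a wording change that uses data already planned and needs no extra participants. When all packages are truly at 85% or more, the chance of GO is essentially unchanged (92% at 85%, 99.8% at 90%). The limitation is imprecision: with 4/5/3 sessions, a package truly at 50% still passes in about 44% of trials (down from about 90%), and one truly at 40% in about 12% (down from about 70%).

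Requiring 80% in every subgroup would be stricter, but it cuts GO from 92% to 58% when every package is truly at 85%. It is not recommended as the default.
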